**Fig. 1 fig1:**
[figure not shown]
Flowchart and treatment allocation in the trial.

## Analysis

7

### Descriptive statistics

7.1

We use and present descriptive statistics to ensure that the reader can evaluate if the sample is reproducible. For categorical variables numbers and percentages will be presented, and Fischer's exact or *χ*^2^-test will be used to assess if there is a difference between the groups defined by way of the exposure variables. For normally distributed variables, the mean and standard deviation will be presented, and ANOVA will be used to assess if there is a difference between the methadone dose groups. For non-categorical and non-normal distributed variables, median and interquartile ranges will be presented, and the Kruskal-Wallis test will be used to assess if there is a difference between groups.

### Primary analysis and treatment assignment

7.2

This trial uses the Bayesian continual reassessment method, therefore stopping guidelines and probabilistic priors in relation to toxicity MTD (maximal tolerable dose) need to be determined before inclusion of the first patient. The stopping rules for the trial include:•If 40 persons are included.•If the probability of the lowest dose exceeding a predetermined toxicity threshold (set at 0.10) is greater than 95 % and more than 10 persons are included.•If the 95 % credibility interval of the toxicity level for the MTD is between 0 and 0.10 (a clinically acceptable toxicity level) and more than 10 persons are included.•If all the above stopping rules are fulfilled and 10 participants are included.

The predetermined toxicity threshold for the lowest dose considers the assumption that toxicity increases with higher doses. Thus, if the toxicity at the lowest dose surpasses the clinically acceptable level of 0.10, further dose escalation should be avoided. The pre-specified prior to this analysis consists only of presumed toxicity levels of the different doses and the alpha parameter. The presumed toxicity levels for the three doses is set to 0.05, 0.1, and 0.2 for 0.10 mg/kg, 0.15 mg/kg, and 0.2 mg/kg, respectively, and alpha follows a *γ*(1*,* 1) distribution. After the specification of the prior and stopping rules, the method uses the dose-response curve to escalate or deescalate the doses in a non-conservative manner (see Fig. 2) and close arms if one or more stopping rules are met. The 1-parameter model estimates the MTD more efficiently by escalating through the doses faster [16]. This is acceptable because the risk of adverse events by respiratory depression is low. Furthermore, there may be difficulties fitting the model or obtaining consistent estimates of model parameters in a two-parameter model [16]. Thus, we choose to use the 1-parameter model for this study.

**Fig. 2 fig2:**
[figure not shown]
CRM output.

### Secondary analysis

7.3

The analysis of the secondary outcomes will consist of:•Survival analysis focusing on the length of stay at the PACU. Kaplan Meier curves will be presented and pseudo-observations together with linear regression will be used to assess if the length of stay at the PACU differs between the three dose levels [17]. If the fit of the linear regression is not satisfactory, then bootstrapped confidence intervals and p-values will be presented instead of their parametric counterparts.•Poisson regression will be used to investigate whether the number of times administration of Naloxone was necessary is dependent on the given dose level. The model control will be a graphical assessment of the deviance residuals. If the model control yields an unsatisfactory fit a negative binomial regression will be used instead.•In relation to postoperative opioid consumption generalized estimating equations will be used as the variability is partially determined by the hospitals infrastructure, which is not reproducible. The p-value will be based on the contrast as time can be a potential effect modifier of the exposure. If convergence issues regarding the maximum likelihood estimate are present then a Poisson or negative binomial regression with clustered standard errors will be performed instead, depending on the distribution of the deviance residuals.•Presence of opioid-related side-effects will be analysed by way of generalized estimating equations with a logit link function, as the variability is connected to the given hospital and therefore not reproducible. The p-value will be based on the contrast as time can be a potential effect modifier of the exposure. If convergence issues regarding the maximum likelihood estimate is present then a logistic regression with clustered standard errors will performed instead.

Postoperative pain will be analysed by way of a mixed effect model with bootstrapped confidence intervals, as the outcome is a Likert scale and the variability is fully determined by the given and is thus reproducible in other settings. The p-value will be based on the contrast as time can be a potential effect modifier of the exposure.

All the outcomes analysed by generalized linear mixed effect models or generalized estimating equations will be presented with margin plots to assess if there is a clinically significant difference between the groups. Conversely, if some effect measures yield a clinically insignificant difference between the exposure groups, strong predictors will be adjusted in the regression analysis to avoid bias for safety measures [18]. In order to avoid potential conservative bias as described by Möller et al. [18], clinically non-significant analyses will be conducted adjusted for strong predictors. The fundament for the evaluation of this bias is explicitly based on clinical expertise to eliminate the risk of analyses driven by statistical significance. In the literature e.g. a clinically relevant reduction in opioid consumption is set to 10 mg of morphine equivalent or a 30 % reduction [19].

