### Secondary outcomes

6.3

The secondary outcomes include:•Length of stay, defined as the number of hours spent at the PACU.•Number of times administration of antidote Naloxone was necessary.•Consumption of opioid rescue medication measured upon arrival at the orthopaedic ward and after 6, 24, and 72 h postoperatively.•Opioid-related side effects, including post-operative nausea and vomiting (PONV), measured upon arrival at the orthopaedic ward and after 6 and 24 h postoperatively.•Postoperative pain will be measured using VRS upon arrival at the orthopaedic ward and after 6, 24, and 72 h postoperatively.

The primary and secondary outcomes will be measured by trained healthcare personnel at the orthopaedic department and recorded in RedCap (Research electronic data Capture). In addition, [name] will note the starting dose and whether the patient experienced toxicity in the dose-escalation program.

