### Exposure

6.4

The exposure is a categorical variable where the groups are defined as:•0.10 mg/kg methadone at the beginning of surgery.•0.15 mg/kg methadone at the beginning of surgery.•0.20 mg/kg methadone at the beginning of surgery.

When patients are included from the ED the orthopaedic doctor will contact the primary investigator [name], who will assign each patient to a methadone group (0,10 mg/kg, 0,15 mg/kg or 0,20 mg/kg) using the model-based Continual Reassessment Method (CRM). This method uses registered primary outcome from the previous included patients or the prespecified prior if no data has been collected (see Fig. 1). The assigned methadone group is registered into REDcap and will be used to estimate the individual dose of methadone, which is calculated by multiplying methadone group with patient weight. This individual methadone dose will be written on a case report file (CRF). The primary care provider from the ED is responsible for withdrawing study medicine and placing the syringe near the patient together with the CRF. The individual dose of methadone is administered intravenously by the certified registered nurse anaesthetist when anaesthesia is commenced. The CRF will follow the patient to the orthopaedic ward.

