### Sample size calculation

7.4

To calculate a sufficient sample size for the primary analysis we choose the formula presented by Kuen Cheung et al. [20]. We set the target toxicity level to 0.10, an accuracy of 0.6 and an odds ratio to 2, as this is a fragile population. Therefore the project will include 40 patients unless the maximum tolerable dose meets the pre-specified stopping rules.

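### The naloxone Poisson model has no provision for a dose group without events, where its per-level rate ratio is not estimable and the default Wald p-value is near 1

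*SAP article*

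**What the plan says.** Section 6.3 of the SAP article lists as a secondary outcome: "Number of times administration of antidote Naloxone was necessary". Section 7.3 gives its analysis: "Poisson regression will be used to investigate whether the number of times administration of Naloxone was necessary is dependent on the given dose level". The check is also fixed: "The model control will be a graphical assessment of the deviance residuals". So is the remedy: "If the model control yields an unsatisfactory fit a negative binomial regression will be used instead".

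Dose enters as three groups; section 6.4 states that "The exposure is a categorical variable where the groups are defined as" 0.10, 0.15 and 0.20 mg/kg. Table 2 has a block for incidence rate ratios with 95% intervals and p-values, with 0.10 mg/kg as reference, but no row for naloxone. Section 7.5 calls a two-sided p below 0.05 significant and requires a 95% interval with each effect size.

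On size, section 7.4 says that "the project will include 40 patients unless the maximum tolerable dose meets the pre-specified stopping rules". On event frequency, section 7.2 says of respiratory depression that "The presumed toxicity levels for the three doses is set to 0.05, 0.1, and 0.2". To justify fast escalation it adds: "This is acceptable because the risk of adverse events by respiratory depression is low". No naloxone rate is given anywhere.

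**The concern.** A Poisson rate ratio needs at least one event in both groups compared. With about 13 patients per dose and an uncommon event, that cannot be taken for granted. In section 7.3 the bullets on opioid consumption and on side effects each have a fallback for convergence problems. The naloxone bullet has only a fallback triggered by poor residuals, which addresses overdispersion and not an empty group.

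Naloxone use bears directly on tolerability. If naloxone were needed only at higher doses, a table of per-level ratios could show an enormous or missing ratio with p close to 1, and a reader could take the result as showing no dose effect.

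**Working it through.** **Plan's own figure.** None is stated for this analysis, so there is nothing to reproduce. Naloxone risk is an assumption, taken below as half, equal to or double the presumed 0.05/0.10/0.20, with one administration per treated patient.

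**1. How often a group has no event.** With illustrative groups of 13/13/14, P(no event) = (1 − p)^n.

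| Assumed risk | 0.10 mg/kg | 0.15 mg/kg | 0.20 mg/kg | Some group has none | 0.10 mg/kg has none, a higher dose has some |
|---|---|---|---|---|---|
| Half | 0.975^13 = 0.720 | 0.95^13 = 0.513 | 0.90^14 = 0.229 | 89% | 64% |
| Equal | 0.95^13 = 0.513 | 0.90^13 = 0.254 | 0.80^14 = 0.044 | 65% | 51% |
| Double | 0.90^13 = 0.254 | 0.80^13 = 0.055 | 0.60^14 = 0.001 | 30% | 25% |

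For the middle row, some group has none with probability 1 − (1 − 0.513)(1 − 0.254)(1 − 0.044) = 0.65. The last column is 0.513 × (1 − 0.254 × 0.044) = 0.51.

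Group sizes will in fact follow the continual reassessment method (CRM). In simulations of that allocation under the presumed toxicities, a treated dose group had no naloxone event in 82 to 86%, 64 to 67% and 44% of trials at half, equal and double risk. The picture is similar.

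**2. What the model then returns.** With one event per patient at most, the log rate ratio has standard error √(1/y_ref + 1/y_dose). As y_ref goes to 0, the log ratio grows only like −ln(y_ref) while the standard error grows like 1/√y_ref. Their quotient therefore goes to 0 and the Wald p-value goes to 1. Refits, for 0.20 against 0.10 mg/kg (the likelihood-ratio test is overall, 2 df):

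| Group sizes | Events | Poisson Wald p | Negative binomial Wald p | Likelihood-ratio p, same Poisson model |
|---|---|---|---|---|
| 10/17/12 | 0/0/4 | 0.999 | 0.999 | 0.009 |
| 13/13/14 | 0/0/5 | > 0.999 | 0.999 | 0.005 |
| 13/13/14 | 0/0/8 | > 0.999 | 0.999 | 0.0002 |

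The first likelihood-ratio value by hand: under no dose effect the top group expects 4 × 12/39 events, so the statistic is 2 × 4 × ln(39/12) = 9.43, and p on 2 df is exp(−9.43/2) = 0.009. The size of the printed ratio depends only on where the software stops iterating.

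**3. Whether the safeguards catch it.** Deviance residuals run from −0.82 to 0.93 for 0/0/4 and from −0.85 to 0.88 for 0/0/5, which is unremarkable. The negative binomial model has the same log-link mean, so its ratio diverges too.

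**4. How often a signal is at stake.** With groups of 13/13/14 at the presumed risks, I summed binomial probabilities over all outcomes with no event at 0.10 mg/kg and an overall likelihood-ratio p below 0.05. The total is about 13% of trials.

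**The case against.** The strongest reply is that the SAP names neither a Wald test nor per-level p-values for naloxone. It asks only whether the count depends on dose. A likelihood-ratio test from the planned model answers that and shows the signal. Table 2 has no naloxone row, so a rate ratio against 0.10 mg/kg is inferred from the model and the layout of the other rows. This stands. A reader might infer that the plan as written will tabulate a clear top-dose excess as not significant, but the document does not commit to that. It leaves the default open.

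A reader might also infer that the analysis will usually fail. That rests on an assumed rate. The low-risk remark in section 7.2 is about respiratory depression and the choice of CRM model, not naloxone, and at double the presumed risk some group is empty in only about 30% of equal-split trials.

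Nor is every empty reference a hidden signal. In the 0/0/4 example, the exact pairwise comparison of 4/12 with 0/10 gives (12/22)^4 = 0.089 one-sided, and adding (10/22)^4 = 0.043 gives 0.13 two-sided. An exact method would also call that single contrast not significant. The evidence lies in the overall comparison.

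Finally, the outcome is secondary, section 7.3 rests interpretation on clinical expertise, and an unbounded interval would be visible. All true, but none of this makes the ratio or its required interval usable, and the stated check and fallback do not address the problem.

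**Conclusion.** The point holds in a limited form and merits a change before analysis. The SAP fixes a model, a check and a fallback that do not deal with a dose group without events. In that case the ratio against an empty 0.10 mg/kg group is not estimable and its default Wald p-value carries no information. If the empty group is a higher dose, the ratio goes to 0, again with p near 1.

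At half, equal or double the presumed toxicity risks, some group is empty in about 89%, 65% or 30% of trials with groups of 13/13/14. An empty reference together with a likelihood-ratio p below 0.05 occurs in about 13% at the presumed risks. These figures rest on the assumed naloxone rates, one administration per patient and near-equal groups.

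The defect is in the per-level ratio and p-value, not in every use of the Poisson model. A reader might go further and conclude that it could falsely establish tolerability. The document does not support that, because the maximum tolerable dose comes from the CRM on respiratory depression, which this leaves untouched.

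**What to change.** In section 7.3, replace the naloxone bullet with the following:

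- Report, for each dose given, the number of administrations and the patients given naloxone as x/n, with exact 95% intervals.
- Base the p-value on a two-sided likelihood-ratio or exact conditional test, overall or for trend across the doses given, and choose which in advance. Do not use per-level Wald tests.
- Give a rate ratio only where both groups have at least one event. Otherwise give a one-sided exact or penalised-likelihood limit.
- Add a naloxone row to Table 2 in this form.

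The cost is SAP wording and a few lines of code, with no change to conduct or sample size. Intervals will be wide, and there will be one overall p-value instead of two. The p-values will be approximate, because dose assignment depends on earlier patients' outcomes and one patient may receive naloxone more than once. For the first of these reasons a simple permutation of dose labels would not be strictly exact either, and the SAP should say so.

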## Objective

4

The trial estimates the maximal tolerable dose by investigating the risk of respiratory depression in the first 24 h after surgery for patients *≥* 60 years undergoing surgery for a hip fracture. The secondary objectives include how the methadone doses are tolerated in regard to side effects and consumption of rescue medication.

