### Reporting and interpretation of statistical measures

7.5

The adaptive dose-finding trial will use probabilistic methods. Therefore, 95 % credibility intervals will be reported in relation to the MTD and the prevalence of the given dose. In the secondary analysis, a p-value below 0.05 will be considered statistically significant, and 95 % confidence intervals will be reported together with their corresponding effect size. All p-values will be two-sided, and no adjustment for multiple testing will be utilized (as these analyses are not the primary analyses). All results will follow the Extended CONSORT guidelines for dose-finding studies if they are available [21].

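### The logit GEE for side effects, and its fallback, give no usable odds ratio, interval or p-value when a small dose group has no events or all events at a time point

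*SAP article*

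**What the plan says.** Section 4 makes side effects part of the trial's second aim: "The secondary objectives include how the methadone doses are tolerated in regard to side effects". Section 7.3 fixes the model: "Presence of opioid-related side-effects will be analysed by way of generalized estimating equations with a logit link function". It adds: "The p-value will be based on the contrast as time can be a potential effect modifier of the exposure". Table 2 shows what this produces: an odds ratio, 95% CI and p-value for 0.15 and 0.20 mg/kg against 0.10 mg/kg at each of three times. (Section 6.3 has side effects "measured upon arrival at the orthopaedic ward and after 6 and 24 h postoperatively", whereas Table 2 lists 6, 24 and 72 h. Either way there are three times and nine dose-time cells.)

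The only contingency is: "If convergence issues regarding the maximum likelihood estimate is present then a logistic regression with clustered standard errors will performed instead".

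On numbers, section 7.4 says: "Therefore the project will include 40 patients unless the maximum tolerable dose meets the pre-specified stopping rules". Two stopping rules in section 7.2 can end the trial early, once their criterion is met "and more than 10 persons are included". Dose groups are filled by the CRM (section 6.4), so their sizes are neither fixed nor balanced. In section 7.5, "a p-value below 0.05 will be considered statistically significant", two-sided and without multiplicity adjustment.

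The SAP does not state the type of standard error, the test statistic or the working correlation for the GEE. Nothing covers a cell in which no patient, or every patient, has a side effect.

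**The concern.** A model that lets the dose effect differ by time estimates each dose-time cell essentially on its own. With 40 patients or fewer over three unequal groups, a cell of about five patients with no event is an ordinary chance result. The fitted log-odds for that cell then diverges, and the reported p-value depends on how the standard error is computed rather than on the evidence. A handful of event-free patients could be reported as a highly significant dose effect, or a dose contrast could be reported with an interval that conveys nothing. Section 8 says the dose found here feeds a later randomised trial, so readers will look at this tolerability table.

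**Working it through.** **Inputs.** From the SAP: maximum N of 40 (taken as stated; the formula behind it is not printed), three doses, three times, reference 0.10 mg/kg, two-sided 0.05. The SAP gives no side-effect rate, so rates of 10% to 50% are assumed.

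**Step 1: standard error of an empty cell.** Take n patients in a cell with no events and let the fitted probability p go to 0.
- Robust variance of the log-odds: n·p² / (n·p·(1−p))² = 1/(n·(1−p)²), which tends to 1/n and so stays finite.
- Model-based variance: 1/(n·p·(1−p)), which tends to infinity.

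The estimate diverges in both cases. The test statistic therefore goes to infinity with robust errors and to zero with model-based errors. A full cell behaves the same way with the sign reversed.

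**Step 2: 0/5 at one dose v 3/15 at the reference.** The reference cell contributes n/(x(n−x)) = 15/(3×12) = 0.417. The robust SE is √(1/5 + 0.417) = √0.617 = 0.785. Fits to example data of 40 patients (groups 15/20/5) gave:

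| Analysis | log-OR | SE | p |
|---|---|---|---|
| GEE, independence, robust | −22.2 | 0.785 | <0.0001 |
| GEE, independence, model-based | about −22 | about 58,590 | 1.0 |
| Fallback: logistic, clustered errors | −12.2 (where iteration stopped) | 0.82 | <0.0001 |
| Fisher's exact | – | – | 0.54 |

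The GEE software reported convergence. An exchangeable working correlation also converged, at a log-OR of −26.2 with a robust p near 0.

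A full cell, 5/5 at the reference v 12/20, has robust SE √(1/5 + 20/(12×8)) = √0.408 = 0.639 and p near 0. Fisher gives p=0.14. With a reference-coded interaction some fits returned erratic SEs (56, 246) or none at all.

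**Step 3: how often an empty cell occurs.** The chance is (1−rate)ⁿ. For n=5 it is 59%, 33% and 17% at rates of 10%, 20% and 30%. For n=10 it is 35%, 11% and 3%. In CRM allocations simulated with the SAP's presumed toxicities (power model, no limit on dose skipping), median group sizes were 13/17/3, and 66% of trials had a dose group of 1 to 5 patients.

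**Step 4: false positives for one contrast if robust errors are used.** All outcomes were enumerated with equal rates in both groups. When exactly one cell is empty or full, the test rejects; when both are empty or both full, it does not; otherwise the ordinary Wald test applies.

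By hand for 15 v 5 at 20%: P(0/5) = 0.8⁵ = 0.328 and P(0/15) = 0.8¹⁵ = 0.035. P(exactly one empty) = 0.328×0.965 + 0.035×0.672 = 0.340. Full cells and ordinary rejections bring the total to 35%.

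| Patients | 10% | 20% | 30% | 50% |
|---|---|---|---|---|
| 15 v 5 | 56% | 35% | 19% | 7% |
| 10 v 10 | 45% | 20% | 7% | 4% |
| 13 v 14 | 37% | 10% | 5% | 5% |

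Fisher's test over the same settings rejects in 0.1% to about 3%.

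**The case against.** **A reader might infer that the plan prescribes robust Wald tests and will therefore report false significance.** The SAP does not say so. Clustered errors are named only for the fallback. Robust errors are customary for a GEE, but model-based errors are not excluded, and with them the same cell gives p near 1. The fits here were not run in Stata 17, which section 7.8 names, and other software may drop the cell or fail visibly. A silent p<0.0001 is one possible outcome, not the certain one. This limits the claim but does not rescue the plan, because none of the possible outcomes is a valid result.

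**A reader might also infer that the fallback is the identical estimator, or that its trigger has no meaning.** The first is true only under working independence. Under another working correlation the fallback is a different estimator that shares the infinite estimate. Under working independence the estimating equations are the logistic likelihood equations, so the trigger does have meaning. What stands is that the fallback does not cure the problem and may not be reached.

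**The size rests on assumed rates.** This is correct. If any opioid-related side effect counts and about half of patients have one, balanced groups show essentially no excess (5% for 13 v 14). If both compared cells are empty, no false positive follows.

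**The consequences are contained.** The MTD and dose assignment depend only on the CRM for respiratory depression. Section 7.3 also calls for margin plots and clinical judgement, and an odds ratio near e⁻²² would be conspicuous. Plots may prompt a second look, but they do not repair the interval and p-value that Table 2 is set up to print.

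**Conclusion.** The point holds for the secondary side-effect analysis. With at most 40 CRM-allocated patients over nine dose-time cells, empty cells are likely at low to moderate side-effect rates, and full cells are possible. Whenever one compared cell is empty or full and the other is not, the planned odds ratio, interval and p-value are unusable: p is near 0 under robust or clustered errors and near 1 under model-based errors. The fallback repeats the infinite estimate.

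The false-positive rates apply only if robust errors are used and only at the assumed rates. They run from 56% (15 v 5, 10% rate) down to the nominal 5% (13 v 14, 30% or 50% rate). The primary analysis and the MTD are not affected.

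**What to change.** In section 7.3, replace the GEE test for side effects and its fallback with Firth-penalised logistic regression fitted separately at each time, reporting a profile-likelihood 95% CI and p-value. Each patient then contributes one record per fit, so no within-patient correlation has to be modelled. The adjustment for strong predictors foreseen at the end of section 7.3 also remains possible. For unadjusted contrasts, Fisher's exact test with an exact CI for the odds ratio is an alternative, but it cannot carry covariates. In Table 2, show events/patients for every dose-time cell.

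The change is one of wording and analysis code and needs no new data. The cost is slight shrinkage of the estimates and loss of the joint dose-by-time model.

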## Discussion

8

The results of this study will provide important evidence on the analgesic safety measures of methadone during hip surgery. The maximal tolerable dose will be used in a future randomized clinical trial. This knowledge is essential when aiming to improve the treatment of hip-fracture patients. The study will run in a real-life setting to increase the feasibility of implementing the methods afterwards. This pre-defined SAP is essential to increase the study's transparency and explicitly describe protocol deviations to increase reproducibility and avoid any risk of reporting bias or data-driven analysis.

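### Secondary comparisons are adjusted for strong predictors only when the observed difference looks clinically unimportant: a result-dependent, one-directional rule that tends to add positive findings

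*SAP article*

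**What the plan says.** Section 7.3 (Secondary analysis) says that outcomes analysed by mixed models or generalized estimating equations "will be presented with margin plots to assess if there is a clinically significant difference between the groups". It continues: "if some effect measures yield a clinically insignificant difference between the exposure groups, strong predictors will be adjusted in the regression analysis". The rule is then repeated: "clinically non-significant analyses will be conducted adjusted for strong predictors". The stated motive is to avoid bias on safety measures, and the judgement is said to be "explicitly based on clinical expertise to eliminate the risk of analyses driven by statistical significance".

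The only threshold is an example for one outcome: "a clinically relevant reduction in opioid consumption is set to 10 mg of morphine equivalent or a 30 % reduction". The strong predictors are not named. The section does not say whether an adjusted result replaces the unadjusted one or is reported beside it.

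Section 7.5 sets the inferential standard: "In the secondary analysis, a p-value below 0.05 will be considered statistically significant", and "All p-values will be two-sided, and no adjustment for multiple testing will be utilized". Section 7.7 places the assessment of effect measures after the analyses. Section 8 gives as a purpose of the SAP to "avoid any risk of reporting bias or data-driven analysis".

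**The concern.** Whether a comparison is adjusted depends on what the comparison shows. A small observed difference gets a second look with covariates; a large one is accepted as it stands. Three consequences follow.

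- The reported p-value or interval comes from a model picked by the result, so it need not have its nominal error rate.
- A large unadjusted difference that owes something to chance imbalance in a strong predictor is never re-examined. With at most 40 patients over three doses (section 7.4), such imbalance is to be expected.
- With predictors unnamed and a threshold given for one outcome in two forms (absolute and relative), further choices remain open after the data are seen.

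At stake are the secondary dose comparisons laid out in Table 2.

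**Working it through.** The plan states no figure on this point, so there is none to reproduce. The check has a reading of the text and a simulation.

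**Reading.** Results are fitted and plotted, the difference is judged, and adjustment follows if it is judged small (section 7.3); section 7.7 confirms that effect measures are assessed after the analyses. The trigger is therefore the observed effect. Judging that effect by clinical relevance rather than by its p-value leaves the choice data-dependent, which is what section 8 says the SAP exists to prevent.

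**Simulation.** Inputs from the SAP: 40 patients, three dose groups, two-sided 0.05, trigger at 10 mg. Assumed, because the SAP does not give them: normal outcome; SD 8, 12, 15 or 20 mg; two predictors with R² 0.3 or three with R² 0.5; groups of 13/13/14 or 6/10/24. The contrast is highest against lowest dose by least squares, with no true difference and 10,000 trials per setting. The Monte Carlo standard error near 5% is √(0.05 × 0.95 / 10,000) = 0.22 percentage points.

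*Added*: positive if the unadjusted test is significant, or if the trigger fires and the adjusted test is significant. *Replaced*: the adjusted test stands whenever the trigger fires.

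Percentage of null trials with p < 0.05, groups 13/13/14:

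| SD (mg) | R² | Always unadjusted | Always adjusted | Rule, added | Rule, replaced | Lost by replacing | Gained by replacing |
|---|---|---|---|---|---|---|---|
| 8 | 0.3 | 5.12 | 5.09 | 7.68 | 5.10 | 2.58 | 2.56 |
| 8 | 0.5 | 4.71 | 5.10 | 8.22 | 5.14 | 3.08 | 3.51 |
| 12 | 0.3 | 5.12 | 4.88 | 7.64 | 6.10 | 1.54 | 2.52 |
| 12 | 0.5 | 5.16 | 4.76 | 8.28 | 6.52 | 1.76 | 3.12 |
| 15 | 0.3 | 4.75 | 4.78 | 6.72 | 6.59 | 0.13 | 1.97 |
| 15 | 0.5 | 5.02 | 5.23 | 7.98 | 7.75 | 0.23 | 2.96 |
| 20 | 0.3 | 4.70 | 4.97 | 5.75 | 5.75 | 0.00 | 1.05 |
| 20 | 0.5 | 4.71 | 4.76 | 6.46 | 6.46 | 0.00 | 1.75 |

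With groups of 6/10/24 the error was 5.68% to 8.57% (added) and 5.12% to 7.75% (replaced). Over all 16 settings, the two fixed analyses stayed between 4.7% and 5.3%.

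**Why losses depend on the SD.** The smallest significant unadjusted difference is about t × SD × √(1/n₁ + 1/n₃), with t = 2.026 on 40 − 3 = 37 degrees of freedom. For 13 against 14 this is 2.026 × 0.385 × SD = 0.780 × SD: 6.2 mg at SD 8, 9.4 at SD 12, 11.7 at SD 15 and 15.6 at SD 20. Only below SD 10/0.780 = 12.8 mg do just-significant results fall under the 10 mg trigger and so face re-fitting. For 6 against 24 the factor is 2.026 × 0.456 = 0.925 and the crossing point is 10.8 mg.

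**Calls of clinical significance.** These cannot fall under either reading, because a difference of 10 mg or more is never re-fitted while a smaller one may cross 10 mg on adjustment. Examples: 7.9% rising to 9.5% (SD 15, 13/13/14, R² 0.3), and 27.3% to 34.0% (SD 20, 6/10/24, R² 0.3).

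**The case against.** The strongest defence is the stated safety purpose. The rule is meant to stop a harm signal being missed through conservative bias, which explains why it works in one direction. That motive is legitimate but does not need a conditional rule. With a true difference of 7 mg, SD 8 mg, R² 0.5 and groups of 13/13/14, power is 59.0% unadjusted, 84.0% always adjusted and 84.2% under the rule with replacement; at SD 12 mg the figures are 31.6%, 52.3% and 55.1%. Unconditional adjustment delivers nearly all of the gain. The rule also covers opioid consumption, where a positive finding is a benefit.

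Second, the simulation is not the planned analysis. Consumption is to be modelled by generalized estimating equations and reported as incidence rate ratios at several times, and the 10 mg figure applies to that outcome alone. This stands: the percentages are illustrative and should not be multiplied over Table 2.

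Third, a reader might infer that the rule can only add significant results and never remove one. The documents do not support that, because they leave replacement open, and under replacement 2.6% of null trials lost significance and 2.6% gained it at SD 8 mg and R² 0.3 (13/13/14).

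Fourth, because dose is assigned by the continual reassessment method and not by randomisation, a reader might infer that large unadjusted differences are confounded. Under section 6.4 the dose depends on earlier patients' outcomes, not on the patient's own age, ASA class or opioid use. Systematic imbalance would have to come through calendar time, and the simulation contains none. That argument is untested and is not relied on here.

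**Conclusion.** The point holds in moderate form. Section 7.3 lets the observed effect decide whether a secondary comparison is adjusted, in one direction only, and this contradicts the aim in section 8. The rule tends to favour added positive findings: per-contrast error of roughly 5% to 8.5% against 5% for either fixed analysis. The size rests on the assumed SDs, R² values and group sizes, on the least-squares stand-in, and on whether the adjusted result adds to or replaces the unadjusted one. At the low end (replacement, SD 8 mg, 13/13/14) there is no detectable inflation.

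A reader might go further and doubt the trial's main result. The documents give no ground for that: the adjustment rule sits in the secondary analysis, and the dose-finding model, the stopping rules and the MTD do not use it.

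**What to change.** Replace the two conditional sentences in section 7.3 with a rule that does not depend on the result:

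- Name a short list of baseline predictors from Table 1 (for example age, ASA class and chronic opioid use), and fix their coding.
- Adjust the model for each continuous or repeated secondary outcome for that list, whatever the unadjusted difference shows.
- Report the unadjusted estimate alongside for every outcome, and state which of the two is the main one.
- For sparse binary or count outcomes (naloxone, rare side effects), state in advance that the unadjusted model, or a model with one named covariate, is used.

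Margin plots and clinical thresholds can stay as aids to interpretation, but should no longer select the model. The cost is a few sentences of SAP wording, since the variables are already in Table 1, and a few degrees of freedom in at most 40 patients. The change should be dated before the secondary outcomes are examined by dose.
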